## Background

Since 1997, when the World Health Organization (WHO) described obesity as a chronic pathology with such an increasing incidence that it can be defined as a global epidemic, obesity is still an increasingly worrying issue for public health authorities. In 2005, about 1.6 billion adults (above 15 years of age) were estimated to be overweight, whereas about 400 million people were obese. WHO further projects that by 2015, approximately 2.3 billion adults will be overweight and more than 700 million will be obese [1]. Obesity is associated with early death [2,3] and is universally recognized as a risk factor for many health complications such as cardiovascular diseases, some types of cancer, osteoarthritis, hypertension, dyslipidemia, hypercholesterolemia and diabetes. Obesity is a strong risk factor for the development of type II diabetes [4,5]. Indeed, as BMI (Body Mass Index) increases, the risk of developing type 2 diabetes increases in a "dose-dependent" manner [6,7]. The prevalence of type 2 diabetes is 3-7 times higher in obese than in normal-weight adults, and those with a BMI >35 are 20 times more likely to develop type 2 diabetes than those with a BMI between 18.5 and 24.9 [8,9].

Given that obesity and associated type 2 diabetes lead to serious health consequences that in turn weigh heavily on public health care costs, developing effective interventions for substantially reduce weight, maintain weight loss and prevent or manage associated diseases like type 2 diabetes is compelling.

Stand-alone and combined treatment options (dietetic, nutritional, physical, behavioral, cognitive-behavioral, pharmacological, surgical) are available for both clinical and community populations, but clinical practice and research have shown significant difficulties with regard to availability, costs, treatment adherence and long-term efficacy [10]. From a public health strategy point of view, many problems are due to the high costs of these procedures, overall within an enduring care setting. Indeed, the main challenge in the treatment of obesity is to maintain weight loss in the long term [11]. Most overweight and obese individuals regain about one third of the weight lost with treatment within 1 year, sometimes even before the end of the intervention, and they are typically back to baseline in 3 to 5 years [12-14]. Similarly, few patients with diabetes go on taking their prescribed medication entirely as intended [15,16].

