Physical activity takes place once a day except for week-end and consists of group programs (20 subjects) based on postural gymnastics, aerobic activity and walks in the open. Inpatients with specific orthopedic complications carry out individual activities planned by physiotherapists and articulated in programs of physical therapy, assisted passive and active mobilization and isokinetic exercise.

Low to moderate weight losses are expected at the end of the in-patient phase, but it is important to note that weight loss is not the primary goal of the in-patient program and each patient is made clear about this point at the very beginning of the treatment. Beyond the medical management of metabolic risk factors for health such as type 2 diabetes, developing a sense of autonomy and competence are the primary purposes of the in-hospital interventions. Patients are afforded the skills and tools for change and are supported in assigning positive values to healthy behaviors and also in aligning them with personal values and lifestyle patterns.

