In the last week, just before discharge from hospital, participants are instructed for the out-patient phase of the program. They receive a multisensory armband (SenseWear^® ^Pro2 Armband), an electronic tool that enables automated monitoring of total energy expenditure (calories burned), active energy expenditure, physical activity duration and levels (METs) and sleep/wake states duration. Patients are instructed to wear this device on the back of the upper arm and to record data for 36 hours every two weeks in a free-living context. The Armband holds up to 12 days of continuous data which the outpatients are instructed to download into their personal computer and to transmit online to a web-site specifically designed for data storing. Outpatients are also told that they can review their progress using the InnerView^® ^Software which analyzes and organizes data into graphs and reports. Participants are then instructed to use the TECNOB platform, an interactive web-site developed by TELBIOS S.P.A. http://www.telbios.it. The TECNOB web-platform supports several functions and delivers many utilities, such as questionnaires, an animated food record diary, an agenda and a videoconference virtual room. In the "questionnaires" section, patients fill in the Outcome Questionnaire [35] and submit data concerning weight and glycated hemoglobin. In the "food record diary" participants submit actual food intake day by day through the selection of food images from a comprehensive visual database provided by METEDA S.P.A. http://www.meteda.it. The same procedure is also possible through a software called METADIETA (Meteda s.p.a.) previously installed on the outpatients' mobile phones before discharge. Through the mobile phones outpatients maintain the contact with the dietitian who regularly sends them SMS containing syntax codes that METADIETA, the software previously installed into the outpatients' mobile phones, uses in order to visually display the food choices (frequency and portions) outpatients have to adhere according to diet prescriptions. By this way, outpatients can keep a food record diary allowing comparisons between current eating and the recommended hypocaloric diet along the whole duration of the program. The "agenda" allows the patients to remember the videoconference appointments with the clinicians and the days when to fill in the questionnaires. Moreover, the patients can use the "memo" space to note down any important event occurred to him/her in the previous week/month. Indeed, some research indicates that changes in behavior (eating and exercise) often follow discrete moments which have been variably described as life events, life crises, teachable moments or epiphanies [36]. Life events can lead to weight loss but also to weight gain and qualitative research shows that it is not the event per se that results in behavior change but the ways in which this event is appraised and interpreted by the individual [37]. The clinical psychologist has thus the opportunity to discuss with the outpatients about the significant events reported in the "memo" space during the videoconference sessions and cognitively reconstruct dysfunctional appraisals in functional ways. Finally, outpatients are instructed to use the videoconference tool. Thanks to this medium, they receive nutritional and cognitive-behavioral tele-counseling with the dietitian and the clinical psychologist who attended the patients inside the hospital. In particular, just after discharge, participants have 6 videoconference contacts with both clinicians along 3 months. From the 3rd to the 6th month sessions are scheduled every 30 days and then even more spaced up to an interval of 60 days. During tele-sessions, clinicians (psychologist and dietitian) test the outpatients' progress, their mood, the maintenance of the "good alimentary and physical activity habits", the loss/increase of weight and ask about critical moments, especially those ones reported on the "memo" web-space. In particular, tele-sessions with the clinical psychologist aim to consolidate strategies and abilities acquired during the in-patient phase, to improve self-esteem and self-efficacy, to support motivation, to prevent relapse and to provide problem-solving and crisis counseling. On the other hand, dietitian assesses adherence and compliance to dietary therapy with a special focus on normal eating behavior, sufficient fluid intake, hunger and fullness regulation, appropriate eating/etiquette (pace and timing of meals), slow rate of eating, and addresses critical points such as plateau in weight loss or lack of readiness to improve dietary habits.

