
In addition to videoconference, outpatients can further contact clinicians by e-mail. Indeed, each patient is given the possibility to join his clinician beyond the established videoconference contacts in case of urgency or emergency. According to the e-message's content, clinicians choose the most appropriate format for delivering feedback among e-mail or telephone. In order to avoid excessive dependence and to contain costs, a maximum number of 1 not scheduled contact a week is established a priori.

As described, in the outpatient phase of the TECNOB program great relevance is given to the clinicians-patient relationship as an important medium and vehicle of change [18]. After discharge, out-patients begin to experience the autonomy and competence to change they develop during the in-patient phase and inevitably face resistances and barriers. Thanks to videoconferences, out-patients are supported by the clinicians who attended them during the in-hospital phase in exploring resistances and barriers they experience and in finding functional pathways to cope. Furthermore, out-patients are helped to experience mastery in terms of the health behavior change that needs to be engaged.

Participants in the control group will receive the hospital-based treatment and will be asked to respond to the follow-up assessments. No contact will be maintained with them at home and no continuous care will be provided after discharge.

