#### Measurements

Primary outcome measure of the randomized trial is weight in kilograms. Secondary outcome measures are energy expenditure, glycated hemoglobin, binge eating, self-efficacy in eating and weight control, body satisfaction, healthy habit formation, disordered eating-related behaviors and cognitions, psychopathological symptoms and weight-related quality of life. Data will be collected at baseline, at discharge from the hospital (c.a. 1 month after) and after 3, 6 and 12 months from the end of the in-hospital treatment.

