### Psychological and behavioral questionnaires

Participants will complete the following questionnaires at entry to the study, at discharge from the hospital and at 3, 6 and 12-month follow-up time points by postal mail, Differently, the Outcome Questionnaire will be administered electronically through the web-platform before each videoconference session with the clinical psychologist.

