### Statistical analysis

Descriptive statistics (means ± SD, or median and interquartile ranges, as appropriate) will be used to describe the study sample with regard to baseline characteristics. Before selecting the most appropriate statistical tests, assumptions for parametric analyses will be checked. Repeated-measure ANCOVA will be used in order to evaluate the effects of the intervention when data do not violate the parametric assumptions. The mean differences between intervention and control group with 95% confidence intervals will be calculated. Analyses will be adjusted for possible confounders such as gender and age. Also effect modification will be investigated using interaction terms between intervention group and gender and age, respectively. If data violate parametric assumptions, we will use the exact methods with Monte Carlo approximation, a series of non-parametric statistical algorithms that enable researchers to make reliable inferences when data are sparse, heavily tied or unbalanced, not normally distributed, or fail to meet any of the underlying assumptions necessary for reliable results using the standard asymptotic method [50]. The Mann-Whitney test with Monte Carlo approximation will be used for independent measures, the Wilcoxon rank-sum test for repeated measures and the Fisher exact test for categorical variables. Weight data will be analyzed with an intention-to-treat (ITT) approach with dropouts assumed to have regained 0,3 kg per month, an assumption already used in previous studies [12,51]. Differently, missing data in the other variables will be replaced with baseline observation carried forward (BOCF) or last observation carried forward (LOCF) as appropriate, assuming no improvement for non-responders patients. Odds ratios with 95% confidence intervals will be also calculated at each follow-up time-point with respect to: 1) the percentage of participants maintaining or improving weight lost at discharge and 2) the percentage gaining a 5% and a 10% of baseline weight reduction for the TECNOB group in comparison with the control group. Finally, logistic regression will be used in order to find out predictors of treatment success defined as weight loss maintenance at the final follow-up time-point.

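### BOCF and LOCF are offered under one no-improvement assumption for the secondary outcomes, but they treat the inpatient gain in opposite ways and can bias the comparison in opposite directions when dropout is unequal

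*Protocol article*

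**What the plan says.** The Statistical analysis section gives weight a single rule: dropouts are assumed to regain 0.3 kg per month. For everything else, "missing data in the other variables will be replaced with baseline observation carried forward (BOCF) or last observation carried forward (LOCF) as appropriate", and the reason given for the pair of rules is "assuming no improvement for non-responders patients". The article does not say which rule goes with which outcome, or what decides between them.

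The measurement schedule matters here. Under Measurements: "Data will be collected at baseline, at discharge from the hospital (c.a. 1 month after) and after 3, 6 and 12 months", the last three visits being counted from discharge. The questionnaires follow the same visits: "Participants will complete the following questionnaires at entry to the study, at discharge from the hospital and at 3, 6 and 12-month follow-up time points". The month in hospital is common to both arms. Of the controls the Intervention section says: "Participants in the control group will receive the hospital-based treatment and will be asked to respond to the follow-up assessments". It adds that they are not contacted at home and receive no further care after discharge.

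**The concern.** Between baseline and follow-up lies a discharge value taken after a month of supervised diet, training and counselling. For a patient lost after discharge, LOCF fills later visits with that value, or with a 3- or 6-month value if the patient stayed longer. BOCF goes back to the admission value.

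If the assumption means no improvement since baseline, LOCF breaks it whenever there was an inpatient gain. If it means no further improvement since the patient was last seen, BOCF breaks it by removing that gain. Neither reading fits both rules.

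The between-arm estimate for glycated hemoglobin, binge eating or quality of life could therefore depend on which rule is used. The dependence is largest when the arms lose patients at different rates. That is plausible here, because TECNOB patients have scheduled tele-sessions and controls have no contact at home. In addition, either rule puts filled-in values into the analysis as if they had been observed, so standard errors leave out the uncertainty of the imputation.

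**Working it through.** The article gives no figure for the effect of this imputation, so there is none to reproduce. The check is an expected-value calculation in units of the inpatient gain.

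**Inputs**
- Inpatient gain at discharge: set to 1 in both arms (assumption). The article expects a change at discharge only for weight: "Low to moderate weight losses are expected at the end of the in-patient phase".
- Dropout: the Sample size calculation section gives 20% overall, not by arm. Assumed splits with the same average: 10% TECNOB and 30% control, or 15% and 25%.
- True fraction of the gain kept at 12 months: *m* in completers, *q* in dropouts. Taken as 2/3, by analogy with the Background statement on weight: "Most overweight and obese individuals regain about one third of the weight lost with treatment within 1 year". Range checked for *q*: 1/3 to 2/3.
- *L*: the average value that LOCF carries. *L* = 1 if all dropouts leave straight after discharge.

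**Formulas for one arm with dropout *d***
- Truth: (1−*d*)*m* + *dq*
- BOCF: (1−*d*)*m*, so the error is −*dq*
- LOCF: (1−*d*)*m* + *dL*, so the error is +*d*(*L*−*q*)

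**Bias in TECNOB minus control, with the same *q* and *L* in both arms**
- BOCF: (dC−dT)·*q*
- LOCF: −(dC−dT)·(*L*−*q*)
- Gap between the two estimates: (dC−dT)·*L*, at most dC−dT when *L* ≤ 1

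**Within one arm**, *d* = 0.20, *q* = 2/3, *L* = 1: BOCF understates the mean gain by 0.2 × 2/3 = 0.133. LOCF overstates it by 0.2 × 1/3 = 0.067.

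**Between arms, no true difference** (*m* = *q* = 2/3, *L* = 1)

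| Dropout TECNOB / control | Rule | TECNOB | Control | Difference |
|---|---|---|---|---|
| 10% / 30% | BOCF | 0.9 × 2/3 = 0.600 | 0.7 × 2/3 = 0.467 | +0.133 |
| 10% / 30% | LOCF | 0.600 + 0.1 = 0.700 | 0.467 + 0.3 = 0.767 | −0.067 |
| 15% / 25% | BOCF | 0.85 × 2/3 = 0.567 | 0.75 × 2/3 = 0.500 | +0.067 |
| 15% / 25% | LOCF | 0.567 + 0.15 = 0.717 | 0.500 + 0.25 = 0.750 | −0.033 |

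The gaps are 0.20 and 0.10 of the gain. At *q* = 1/3 with 10% / 30%, the biases are 0.20 × 1/3 = +0.067 (BOCF) and −0.20 × 2/3 = −0.133 (LOCF). If the dropout rates are exchanged between arms, all signs swap.

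**Later losses.** Assume linear relapse from 1 to 2/3 and losses spread evenly over the three intervals. The carried values are 1, 0.917 and 0.833, so *L* = 0.917. For 10% / 30%, LOCF gives (0.600 + 0.092) − (0.467 + 0.275) = −0.050. The gap is 0.20 × 0.917 = 0.183.

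**Equal dropout.** At 20% in each arm with equal retention, both biases are zero. If TECNOB patients keep all of the gain and controls 2/3, in completers and dropouts alike, and *L* = 1, the true difference is 0.333. Both rules then give 0.8 × 1 − 0.8 × 2/3 = 0.267. They agree, but both dilute the effect.

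**The case against.** The best defence is that this is loose wording in a condensed article. The full protocol or analysis plan may assign one rule to each outcome, and the assumption may have been meant as no further improvement since the last value, which suits LOCF. The assignment could indeed sit elsewhere. What remains is that the article itself gives one rationale to two rules, and no reading of that rationale covers both. The numerical inputs are also assumptions. With a 0.3-point gain and dropout of 15% against 25%, the gap is 0.10 × 0.3 = 0.03 points. That limit stands.

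Several stronger readings are tempting, and the document does not support them:
- *The rule will be chosen after the data are seen.* The article gives no time for the choice.
- *LOCF always favours the arm that loses more patients, and BOCF the other.* This needs dropouts to keep part but not all of the gain. If they would have gone on improving after discharge, LOCF penalises the arm losing more. If they fall below baseline, BOCF favours that arm.
- *LOCF contradicts the weight rule.* The article presents the secondary-outcome rule as deliberately different from the one for weight.
- *Controls have no energy-expenditure data, so carry-forward would supply all of it.* The Intervention section says of patients being prepared for the outpatient phase, "They receive a multisensory armband", and does not mention controls there. But Measurements lists energy expenditure as a trial outcome with a baseline value, and the Energy expenditure section does not limit it to one arm. At most this is a separate query about data collection.
- *Carried-forward values have no variance.* They vary between patients. What is lost is the uncertainty of the imputation.

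**Conclusion.** The point holds in a limited form. The two permitted rules make different assumptions about a patient lost after discharge, and the single stated justification cannot cover both. They bias the between-arm contrast in opposite directions if dropout differs by arm and dropouts keep part but not all of the inpatient gain. With the same gain and the same average carried value in both arms, and no improvement past discharge, the gap is bounded by the dropout difference times the gain: 0.10 to 0.20 of the gain for the splits assumed here. It is smaller if losses come later.

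The document gives neither dropout by arm nor an expected inpatient gain or SD for any secondary outcome. The size therefore cannot be put in clinical units or standard errors, and a reversed result is a possibility rather than a prediction. The secondary tests are declared exploratory, and the confirmatory weight analysis has its own rule and is untouched. Severity is modest, but the remedy is cheap.

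**What to change.** Replace BOCF/LOCF as the main rule for continuous secondary outcomes with a likelihood-based repeated-measures mixed model on all observed post-baseline values. Include arm, visit and arm-by-visit, and adjust for the baseline value of the outcome.

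Do not adjust for the discharge value. Randomization follows the baseline measurements, and TECNOB patients are equipped and instructed in the last inpatient week, so discharge comes after allocation. The discharge value should enter as one of the responses, where it still informs the model about patients lost later.

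Keep BOCF as a named sensitivity analysis and state its assumption as no improvement from baseline, which is what it imposes.

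The cost is a change of analysis wording, with no extra data collection. Intervals will be slightly wider, because missing values no longer count as observed. The model assumes that data are missing at random, which the BOCF analysis probes.

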For these reasons, we developed TECNOB (TEChnology for OBesity), a comprehensive two-phase stepped down program enhanced by telecare for the long-term treatment of obese people with type 2 diabetes seeking intervention for weight loss [27]. The core aspects of TECNOB are the hospital-based intensive treatment and the continuity of care at home using new information and communication technologies (ICT) such as internet and mobile phones. ICT-based approaches have already been shown to be helpful in weight loss and long-term maintenance [10,12,28-32], but much more work remains to be carried out in order to confirm these findings. Furthermore, very few studies have investigated the effects of an ICT-based program on obese patients with established type 2 diabetes and to our knowledge no study has tested a comprehensive long-term stepped down intervention starting with 1-month hospitalization specifically addressed to weight loss.

TECNOB protocol was mainly framed within the self-determination theoretical model of behavior change [33] and thus emphasizes the importance of maximizing the patients' experience of autonomy, competence and relatedness for the successful maintenance of behavior change [18].

This paper describes the design of the TECNOB study, a two-arm randomized controlled trial (RCT). The aims of this study are to evaluate the effectiveness of the TECNOB program in a sample of obese people with type 2 diabetes seeking treatment for weight reduction and to find out what behavioral and psychological variables are predictive of treatment success.

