#### Sample size calculation

The sample size calculation is based on a difference in weight regain of 3 kg between the intervention and control group after 12 months. The standard deviation of weight regain for the control group is considered to be 6 [12]. Based on these data, 64 participants per group are needed to detect this difference with an alpha of 0.05 two-sided and a power of 0.80. We decided not to make assumptions on sidedness because the TECHNOB program may also have negative effects in comparison with the control group. A sample of 154 persons (n = 77 per group) is required taking into account a dropout rate of 20%.

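### The exploratory predictor analysis models only a yes/no cut of 12-month weight, which wastes power that the collected kilogram data would keep

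*Protocol article*

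**What the plan says.** The end of the Background section sets two aims. One is the effectiveness of the programme; the other is "to find out what behavioral and psychological variables are predictive of treatment success".

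The Measurements section states: "Primary outcome measure of the randomized trial is weight in kilograms". It adds: "Data will be collected at baseline, at discharge from the hospital (c.a. 1 month after) and after 3, 6 and 12 months". A continuous change in weight from discharge to 12 months can therefore be formed for every patient who is followed up.

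The Statistical analysis section uses continuous weight for the arm comparison, and for the interactions of arm with gender and with age. For the predictor aim it names a different model: "logistic regression will be used in order to find out predictors of treatment success defined as weight loss maintenance at the final follow-up time-point". The nearest definition of maintenance is in the preceding sentence, on odds ratios: "the percentage of participants maintaining or improving weight lost at discharge". The article does not expressly tie that definition to the logistic model.

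The same section classes the secondary-outcome tests as explorative, and the Abstract and Discussion present the predictor question as one to be explored.

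**The concern.** Maintenance at 12 months is a threshold on weight. If it means weighing no more than at discharge, a patient who regains 0.5 kg and one who regains 12 kg receive the same outcome value. The planning standard deviation is 6 kg, so those two patients are almost two standard deviations apart. Some information is lost wherever the threshold falls, and the article gives no reason for preferring the cut as the main scale.

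At stake is the chance of detecting real predictors. The sample was sized for the arm difference in weight regain, with no separate provision for this aim. A loss of power here makes a true, moderate predictor more likely to be missed or reported as absent. No conclusion on the treatment effect is affected.

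**Working it through.** **1. The plan's own figure.** The Sample size calculation section uses a "difference in weight regain of 3 kg between the intervention and control group after 12 months" and adds: "The standard deviation of weight regain for the control group is considered to be 6". The standardised difference is 3/6 = 0.5. At two-sided 0.05 and power 0.80, the two-sample t-test needs 63.8, so 64 per group (63 by the normal approximation), and power at 64 is 0.801. This agrees with "64 participants per group are needed to detect this difference with an alpha of 0.05 two-sided and a power of 0.80". No power is given for the predictor aim, so there is no stated figure to reproduce for it.

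**2. Inputs and assumptions.**
- From the article: SD 6 kg; 64 per group evaluable; 154 recruited; 20% dropout; two-sided alpha 0.05.
- Patients analysed: N = 154 × 0.8 = 123 completers, up to 154 if everyone is included.
- Assumed: a predictor's correlation r with regain from 0.10 to 0.40.
- Assumed: a success share p from 20% to 50%. With success taken as regain of 0 kg or less and normal regain with mean m, p = Φ(−m/6). This gives 50% at m = 0, 27% at m = 3.6 and 20% at m = 5.

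**3. Formula.** Continuous scale: power ≈ Φ(atanh(r)·√(N−3) − 1.96). After the cut, r is replaced by r·f, where f = φ(z_p)/√(p(1−p)). The factor f is 0.798, 0.759 and 0.700 at p = 50%, 30% and 20%. Its square is the share of information kept: 64%, 58% and 49%.

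*Example, N = 123, r = 0.25, p = 30%.* Continuous: atanh(0.25) = 0.255; × √120 = 2.80; less 1.96 = 0.84; power 0.80. Cut: r·f = 0.190; atanh = 0.192; × √120 = 2.10; less 1.96 = 0.14; power 0.56. The loss is 24 points.

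**4. Results over the range.**

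| N | r | Linear | Cut, p = 50% | Cut, p = 30% | Cut, p = 20% | Loss (points) |
|---|---|---|---|---|---|---|
| 123 | 0.10 | 0.195 | 0.139 | 0.130 | 0.117 | 6–8 |
| 123 | 0.20 | 0.603 | 0.422 | 0.388 | 0.339 | 18–26 |
| 123 | 0.25 | 0.799 | 0.601 | 0.557 | 0.491 | 20–31 |
| 123 | 0.30 | 0.924 | 0.762 | 0.718 | 0.646 | 16–28 |
| 123 | 0.40 | 0.996 | 0.952 | 0.930 | 0.883 | 4–11 |
| 154 | 0.10 | 0.234 | 0.164 | 0.152 | 0.136 | 7–10 |
| 154 | 0.20 | 0.702 | 0.507 | 0.468 | 0.410 | 20–29 |
| 154 | 0.25 | 0.881 | 0.700 | 0.655 | 0.584 | 18–30 |
| 154 | 0.30 | 0.967 | 0.851 | 0.812 | 0.745 | 12–22 |
| 154 | 0.40 | 0.999 | 0.982 | 0.971 | 0.942 | 2–6 |

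For r = 0.20 to 0.30 the formula gives 12 to 31 points. Simulation of the two regressions over the same settings gives 11 to 32.

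**5. A simulation built on the plan's figures.** Take 64 per arm, SD 6 kg, a 3 kg arm difference, and an assumed control regain of 3.6 kg (0.3 kg × 12 months, borrowed from the dropout rule). Both models are adjusted for arm. Linear against logistic power is 0.63 against 0.42 at r = 0.20, 0.81 against 0.59 at r = 0.25, and 0.94 against 0.76 at r = 0.30. About 47 of 128 patients succeed.

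**6. The plan's dropout rule.** With 77 per arm and 20% lost at discharge and set to +3.6 kg, the loss at r = 0.20 to 0.30 remains about 20 to 27 points (for example 0.78 against 0.54 at r = 0.25). The rule does not remove the problem. Under a maintenance definition based on discharge weight, it also counts every such dropout as a failure.

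**The case against.** The best defence is that the binary outcome is what the aim asks for. The article speaks throughout of predictors of treatment success, defines success as maintenance, and in the Background calls long-term maintenance the main challenge in treating obesity. A linear model answers a somewhat different question: how many kilograms go with a unit of score, as opposed to who maintains. The aim is also exploratory, and the confirmatory test is untouched. All of this stands. It rules out calling the plan contradictory and argues for keeping the logistic model, but it does not justify making the less efficient scale the only one named.

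It may also be said that an article condenses a fuller plan. That covers details such as how variables are selected. It does not cover the model itself, which the article states.

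A reader might go further in three ways that the document does not support:
- **Too few events for the questionnaire scores.** The questionnaires yield many scales, so one might divide the expected successes by their number and predict unstable odds ratios. The article nowhere says that all scores enter one model, and crowding would affect a linear model too.
- **Conclusions on who benefits most rest on this analysis.** The Discussion does link the two. But who gains most from the intervention is a question of effect modification and needs arm-by-predictor terms. Neither the logistic model nor the linear one proposed here would answer it.
- **The whole plan ignores continuous weight below the arm comparison.** Gender and age are examined as effect modifiers alongside the arm comparison of weight. The gap concerns the behavioural and psychological predictors.

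**Conclusion.** The point holds as an inefficiency in an exploratory analysis. For the behavioural and psychological predictors, the only model named uses a yes/no cut of a measure already collected in kilograms.

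The cost is roughly 11 to 32 points of power per predictor if r is 0.20 to 0.30, the success share is 20% to 50%, regain is normal with SD 6 kg, and 123 to 154 patients are analysed. It shrinks to about 2 to 11 points at r = 0.10, where power is low on either scale, and at r = 0.40, where it is high on either. A single unconditional figure would be wrong, because the documents give neither the correlation nor the success rate. The direction does not depend on those values: under the normal model the cut keeps about half to two thirds of the information (49% to 64%).

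**What to change.** In the Statistical analysis section, make the main predictor analysis a linear regression of 12-month weight in kilograms on the behavioural and psychological scores, adjusted for discharge weight and arm. Discharge weight, and not baseline weight, is the right covariate: maintenance runs from discharge, and adjusting for baseline would mix in the weight lost in hospital. Keep the logistic regression of maintenance as the supportive analysis, so that an odds ratio of success is still reported.

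The change is to wording only. It needs no new data, patients or software. The small downside is that the main result reads as kilograms per unit of score, which is less immediate than an odds ratio. The fixed 0.3 kg per month assigned to dropouts affects either model, so this change does not settle how missing weights are handled.
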